#### Participant withdrawal and other drop-outs

Patients may withdraw from the participation for any reason at any time. The patients are not obliged to justify their withdrawal. However, they will be asked about it. Possible reasons may be deterioration of health or consideration of the questionnaires as an additional burden. If the patient does not return the written questionnaire set, we contact the appropriate enrollment person to identify the reason.

### Data management

#### Data organization

Contact and process information are saved in a database which is programmed with Microsoft Access especially for this evaluation (names; address; telephone number; allocation; contact events, outgoing or incoming of questionnaires; date of enrollment; date of dispatch; date of fill out; enrollment person; PN; withdrawal; data entry). The database keeps track the patients’ timeline and allows intervening if the time interval between the patient questionnaires becomes too large (algorithm and alerts). In addition, the database enables the cooperation partners to be kept up to date in terms of recruitment and study process (reports and summaries). Access is multiple times secured for privacy reasons.

#### Data entry and quality

The filled-out questionnaires are scanned with a standard hardware (Fujitsu fi-7140) and analyzed with FORMS Desktop (Lexmark Enterprise Software) which is software to automatic data entry. This procedure allows a fast and accurate data entry. All marks in checkboxes are transferred with a security of 100%. Numeric and alphabetical characters are verified by the study assistant. During the period of data entry, permanent controls and plausibility checks are performed by the data manager.

#### Data security

All electronic data is located in a secure folder on a secure intranet. Only members of the evaluation team get access. The organization database is restricted by passwords. Electronic data is protected against loss by a security procedure of the Jena University Hospital.

According to the German laws regarding clinical studies the paper questionnaires will be kept for 10 years in a safe archive of the Jena University Hospital.

### Statistical methods

Characteristics of control and intervention groups (e.g. age, sex, education, family situation, partner situation) will be analyzed with descriptive statistics. Since no randomization is made for ethical and research practical reasons, univariate tests are used to determine which of the above mentioned characteristics differ between the two groups. Ideally there are no significant differences between the two groups. In the case of significant differences we will compute propensity scores using the corresponding pre-treatment variables. Then, we will apply in the subsequent analyses propensity scores as stabilized regression weights to reduce bias caused by different group characteristics.

The main hypothesis of an intervention effect on psychological and physical health, self-efficacy, health care costs etc. will be proofed by the comparison of averages of intervention and control group (resp. t-tests). To estimate the corresponding regression adjusted group means we will use growth curve models. Furthermore, we will conduct subgroup analyses to identify conditional treatment effects.

For dropout analysis we will conduct a logistic regression with dropout as criterion and group assignment and baseline variables as predictors applying the regression weight mentioned above. For the time-to-event analysis we will conduct a Cox regression.

The level of significance will be α = 0.05. To validate our analyses, we will conduct the analyses with imputed missing data and without imputation.

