**Methods:**

The study population includes all cancer types, both new and existing diseases. PIKKO (with patient navigator, oncological knowledge database, specialized oncological counseling) is evaluated within a controlled, non-randomized, comparative, multicenter, longitudinal design. In addition to patient surveys, data from statutory health insurances and utilization data from the web database are collected, and interviews with patient navigators and doctors are carried out. Patients are assigned to a control (usual care) or an intervention group (u. c. + PIKKO). Primary outcome is the health related quality of life (SF-12) six months after baseline. Secondary outcomes are self-efficacy (GSE), psychological distress such as depression (PHQ-9) or anxiety (GAD-7), health literacy (HLS-EU-Q47) and patient satisfaction in health care (Qualiskope-A). Furthermore, the time course of direct costs of medical care (e.g. work disability days) and usage data of the intervention modules are analyzed. Among other statistical procedures, we use t-tests, univariate tests and growth curve models.

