### Outcomes

#### Primary outcome

The primary outcome is the health-related quality of life (HRQoL) particularly the mental component score measured by the SF-12 questionnaire [28, 29] six months after baseline. Patients underwent intervention are supposed to improve their psychological QoL to a greater extent than patients without intervention (comparison of means of study groups). SF-12 is the valid and tested short form of the SF-36 questionnaire [30]. It is used in many cases of cancer research (e.g. [31, 32]). HRQoL is based on self-report questionnaires filled out by the patients themselves.

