### Sample size calculation

The three participating health insurance companies have a potential of 325,000 insured persons in the Saarland and their averaged prevalence of cancer (ICD-10-diagnosis groups C00-C97 or D45-D48) is 6.532%. Thus, the study population included (rounded up) 22,000 patients.

The financing of the PIKKO supply concept was calculated for a maximum of 1.800 patients per group, 3.600 patients in total. That means that 1.800 participants of the intervention group can benefit from the PN and the other intervention modules.

To evaluate the PIKKO intervention only 676 participants (338 per group) of the patient questionnaires are required to the statistical analyses. This number of cases was calculated with the program GPower version 3.1.7 [41]. The calculation is based on an expected effect of d = 0.25 for a two-sided t-test with same sized comparative groups, a level of significance of α = 0.05 and a power of 1-β = 0.9. The t-test refers to the primary outcome. We assumed that 338 patients would drop out and added this amount to the total number of included patients. As a consequence, the recruiting aim was *N* = 1014 = 676 + 338 patients (per group 507 = 338 reaching the end point + 169 dropout). The expected dropout rate was 33.3% regarding the baseline (338 of 1014) or respectively 50% regarding the patients reached the endpoint (338 of 676).

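### The statistical section tests a multi-outcome main hypothesis by t-tests and does not name one baseline-adjusted six-month SF-12 mental score contrast as the deciding test

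*Protocol article*

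**What the plan says.** All references are to the protocol article.

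- **Abstract, Methods:** "Primary outcome is the health related quality of life (SF-12) six months after baseline". No component score is named.
- **Primary outcome:** SF-12 at six months with emphasis on the MCS. The expectation concerns change: "Patients underwent intervention are supposed to improve their psychological QoL to a greater extent than patients without intervention". The comparison given for it is one of group means.
- **Secondary outcomes:** self-efficacy, depression, anxiety, health literacy, satisfaction, costs and days of inability to work are listed here. The SF-12 physical component score (PCS) is assigned nowhere.
- **Sample size calculation:** one test, with an "expected effect of d = 0.25 for a two-sided t-test with same sized comparative groups", at "a level of significance of α = 0.05 and a power of 1-β = 0.9", so that "only 676 participants (338 per group) of the patient questionnaires are required to the statistical analyses". The section adds: "The t-test refers to the primary outcome".
- **Statistical methods:** the hypothesis is worded as "The main hypothesis of an intervention effect on psychological and physical health, self-efficacy, health care costs etc". On how to test it, the section then says that it "will be proofed by the comparison of averages of intervention and control group (resp. t-tests". Growth curve models are to supply the regression-adjusted means. Propensity scores enter later analyses as stabilized weights if univariate tests find significant group differences; the characteristics given as examples are demographic and social. The significance level is 0.05.
- **Table 1:** SF-12 is collected at T0 and at every follow-up, including T2 (six months).

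**The concern.** Two things do not fit together.

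First, the hypothesis in the statistical section is wider than the primary outcome and the powered test. It takes in outcomes that the article itself lists as secondary, leaves the set open and names no time point. A reader cannot tell from that section which result decides whether PIKKO worked.

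Second, the stated expectation is greater improvement, whereas a t-test of six-month means compares levels. The two agree only if the groups start level. Here the date of recruitment sets the group, and the Trial status section reports that a further insurer joined in summer 2019, after control recruitment had closed on 31 October 2018. A baseline MCS difference is therefore plausible. The planned protection is conditional on significance, does not name baseline MCS, and is not said to take precedence over the t-test. At stake is whether the main result, on which a recommendation for national roll-out is to rest, partly reflects who was recruited when.

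**Working it through.** **1. The plan's own figure.** Inputs from Sample size calculation: d = 0.25, two-sided alpha 0.05, power 0.90, equal groups.

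- Normal approximation: n = 2(1.960 + 1.282)² / 0.25² = 336.2, so 337 per group.
- Exact noncentral t: power is 0.8998 at 337 and 0.9007 at 338, so 338 per group. This reproduces the plan.
- Dropout: 338 / (1 − 1/3) = 507 per group, 1014 in total. This also reproduces.

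The sample size is therefore that of one two-sided test on one outcome.

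**2. What an unadjusted T2 comparison carries.** Let g be the baseline MCS gap in SD units and r the T0–T2 correlation of MCS. The article gives neither, so both are assumptions. With equal SDs at T0 and T2 and no treatment effect, the expected T2 difference is r × g. The false-positive rate is the probability that the two-sided t-test at 338 per group rejects when the true T2 difference is r × g.

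| g (SD) | r | Bias r × g (SD) | Share of d = 0.25 | False-positive rate |
|---|---|---|---|---|
| 0.10 | 0.4 | 0.04 | 16% | 0.081 |
| 0.10 | 0.7 | 0.07 | 28% | 0.149 |
| 0.15 | 0.4 | 0.06 | 24% | 0.122 |
| 0.15 | 0.7 | 0.105 | 42% | 0.276 |
| 0.20 | 0.4 | 0.08 | 32% | 0.180 |
| 0.20 | 0.7 | 0.14 | 56% | 0.443 |

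**3. Would the significance screen catch it?** Suppose baseline MCS were among the screened variables. The probability that a two-sided test at 0.05 flags the gap is:

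| g (SD) | 338 per group | 507 per group |
|---|---|---|
| 0.10 | 0.255 | 0.356 |
| 0.15 | 0.495 | 0.665 |
| 0.20 | 0.738 | 0.889 |

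A 0.10 SD gap would go unweighted about two times in three or more.

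**4. Can the planned sample carry an adjusted contrast?** Adjusting for T0 MCS multiplies the residual variance by 1 − r², so n = 336.2 × (1 − r²).

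| r | n per group for 90% power | Power at 338 per group | n / 338 |
|---|---|---|---|
| 0.4 | 283 | 0.944 | 0.84 |
| 0.5 | 253 | 0.963 | 0.75 |
| 0.6 | 216 | 0.982 | 0.64 |
| 0.7 | 172 | 0.995 | 0.51 |

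The power figures are before any loss from weighting. The last column is the fraction of the sample that must remain effective after weighting to keep 90% power.

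**5. Alpha under the wide wording.** If significance on any of the four named domains counted as success, the error rate would be 1 − 0.95⁴ = 0.1855 for independent tests. With pairwise correlations of 0.3 to 0.7 it would be about 0.17 to 0.13. Under the Primary outcome and Sample size sections it is 0.05.

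**The case against.** The strongest reply is that the article does more than compare raw means. It plans stabilized propensity weights, which it repeats under Limitations as the answer to non-randomization, and it describes the means to be compared as regression-adjusted through growth curves. A reader might infer that any baseline gap passes straight into the reported effect. The article does not support that. What stands is narrower: the weighting is conditional, baseline MCS is not named, and precedence over the t-test is not stated.

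A reader might also infer that alpha is spent repeatedly, with an error rate near 37% for nine independent outcomes (1 − 0.95⁹ = 0.370). That does not hold for the primary outcome. The article names one primary outcome, ties one powered test to it and lists the others as secondary. Testing secondary outcomes at 0.05 does not inflate the primary error rate. Inflation arises only if the wording in Statistical methods is taken as the confirmatory hypothesis.

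Two further inferences fail. Control patients who switch stop contributing control questionnaires, and only data collected up to then count as control data, so post-switch answers do not enter the control curve. Objections to a straight-line time effect or to group-specific intercepts concern a model form that the article does not state and may leave to a fuller plan. The same applies to a complete covariate list.

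Finally, naming only SF-12 in the abstract can be read as shorthand, since the Objectives and Primary outcome sections both point to the mental component. That is fair, but PCS still has no stated place, and the statistical section puts physical health into the main hypothesis.

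**Conclusion.** The point holds in a limited form. The main hypothesis in Statistical methods conflicts with the single primary outcome and single powered test elsewhere, and the article does not fix which estimate decides. A T2 comparison not adjusted for T0 MCS would be biased by 0.04 to 0.14 SD, 16 to 56% of d = 0.25, for gaps of 0.10 to 0.20 SD and r of 0.4 to 0.7. A 0.10 SD gap would be flagged only about 26 to 36% of the time. The gaps and correlations are assumptions, and the direction of any real gap is unknown, so the bias could favour either group. The figures describe what the current wording permits if the unadjusted t-test decides; they do not show that the final analysis would be biased by this amount. The sample size calculation itself is correct.

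**What to change.** Before the outcome data are analysed, state one confirmatory test: the group difference in SF-12 MCS at T2, adjusted for T0 MCS and propensity-weighted regardless of baseline significance tests, at two-sided alpha 0.05. Say that it takes precedence over the unadjusted t-test, which may be kept as a supporting analysis. Class PCS as secondary, alongside the outcomes already listed there. Align the abstract and the Primary outcome, Sample size calculation and Statistical methods sections with this. Formal multiplicity adjustment of the secondary outcomes is optional and not needed for this point.

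The cost is wording only. T0 SF-12 is already collected and the planned 338 per group is enough unless weighting losses exceed the margins shown above. One limit remains: T0 was completed by post in the control group and before the first navigator consultation in the intervention group, so adjustment for T0 also takes in any effect of that difference in collection.

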### Strengths

This new supportive care concept is intended to establish an offer for all cancer patients. Low barriers for the procurement of information such as the website, which offers both specific and general information, are just as much a part of the concept as the broad further training of PN, who can thus advise all cancer patients.

The study is designed to evaluate the effect of PIKKO interventions under naturalistic conditions. The according heterogeneity of the sample (age range, all cancer types, all sexes) tries to reflect the reality of oncological care. Due to the heterogeneity of the sample, subgroup analyses are planned to show which module of PIKKO works best for whom.

Furthermore, the longitudinal design with five measurement points allows the investigation of long-term effects.

Last, the telephone interviews with participating PN and physicians can show experiences in the implementation that help to make PIKKO a common part of cancer care.

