### Limitations

In general, less burdened patients, patients with a stronger self-motivation, patients with higher self-efficacy or patients with more social support could preferably participate, leading to a selection bias. Related with this bias can be an overestimation of treatment effects when the treatment is especially effective for less burdened patients. Also an underestimation of the mortality or patient’s withdrawal is possible. To examine the selection bias, we included a second control group which is a random sample of eligible patients based on health insurance company data. We expect that the selection bias is small so that the generalizability of study results should be high.

The voluntary and selective participation of hospitals (respectively individual departments), clinics and practices could lead to a selective clientele of patient e.g. disproportionately many breast cancer patients. However, this could also make the study more comparable to the many studies that have been pre-determined for certain groups, e.g. specialized in breast cancer patients [18].

Due to ethical and other reasons (described in the section “Trial design”) the design is not randomized. To compensate for this limitation, we will use propensity scores for analyses [58, 59].

Since we will collect questionnaires from seriously ill and elderly patients, we might expect incomplete questionnaires. Missing items and missing complete questionnaires should be compensated by imputation of missing data [44, 45].

Each participant agrees with the use of his data from the statutory health insurance companies. These data are collected from all included patients without their direct participation. However, to collect questionnaire data, we rely on the direct support of the patients. The number of data sets can therefore vary between data from the questionnaires and from the statutory health insurance companies.

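### Choosing propensity variables by whole-group significance, and applying the resulting weight in the subgroup analyses, secures at best overall balance and can leave subgroup contrasts confounded

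*Protocol article*

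**What the plan says.** All references are to the protocol article. The section Statistical methods sets out a sequence:

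1. Screening: "univariate tests are used to determine which of the above mentioned characteristics differ between the two groups". The comparison is between control and intervention as whole groups.
2. Score: "In the case of significant differences we will compute propensity scores using the corresponding pre-treatment variables". If nothing is significant, no score is described.
3. Use: "we will apply in the subsequent analyses propensity scores as stabilized regression weights to reduce bias caused by different group characteristics".
4. The next paragraph lists the analyses that follow: group comparisons, growth curve models ("To estimate the corresponding regression adjusted group means we will use growth curve models") and then "Furthermore, we will conduct subgroup analyses to identify conditional treatment effects". The subgroup analyses are not exempted from step 3.
5. The dropout model reuses the weight in the singular: "applying the regression weight mentioned above".

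No subgroups are named, and the covariates of the growth curve models are not listed. Under Trial design, assignment is by recruitment date, with controls enrolled first.

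**The concern.** Without randomization, a subgroup contrast can be trusted only as far as the two arms are comparable inside that subgroup. A main-effects score fitted to the whole sample balances covariates on average over the sample. If the arms differ in one direction in one subgroup and in the other direction elsewhere, two things go wrong. The differences cancel in the whole-group test, so the covariate usually fails the screen and no weight is built. And if a whole-sample weight is built anyway, it leaves the difference in imbalance between the subgroups where it was.

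At stake is whether a reported conditional treatment effect reflects PIKKO or a difference in case mix. The design leaves room for uneven shifts. The arms are recruited in successive periods, by about 80 physicians of various specializations and through four routes. According to Trial status, a further insurer joined in summer 2019, after control recruitment had closed on 31 October 2018. None of this shows that imbalance does differ by subgroup, but nothing rules it out either.

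**Working it through.** **Inputs from the document (Sample size calculation).** d = 0.25, two-sided alpha 0.05, power 0.90, 338 per group analysed, 1014 recruited.

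**The plan's own figure.** n per group = 2(1.960 + 1.282)²/0.25² = 336.2, so 337 by the normal approximation. The exact t calculation gives 337.2, so 338. Then 338 × 2 = 676, and 676/(1 − 1/3) = 1014. The figures reproduce, and the present point does not depend on them.

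**Assumptions (not in the document).** Two equal subgroups, hence 338/2 = 169 patients per cell. No treatment effect anywhere. One covariate with correlation β = 0.3 or 0.5 with the outcome, and an imbalance between arms of δ1 and δ0 SD in the two subgroups.

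**False interaction.** Its expected size is β(δ1 − δ0). Its standard error is about √(4/169) = 0.154 SD. The rejection rate is about Φ(size/0.154 − 1.96), plus a negligible lower tail.

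| Imbalance (SD) | β | False interaction | Rejection by formula | Simulated, documented rule |
|---|---|---|---|---|
| +0.3/−0.3 | 0.5 | 0.5 × 0.6 = 0.30 | 50% | 0.29–0.31 SD, 46–53% |
| +0.3/−0.3 | 0.3 | 0.3 × 0.6 = 0.18 | 22% | 0.17–0.18 SD, 20–21% |
| +0.2/−0.2 | 0.5 | 0.5 × 0.4 = 0.20 | 26% | 0.19 SD, 23% |
| +0.2/−0.2 | 0.3 | 0.3 × 0.4 = 0.12 | 12% | 0.12 SD, 13% |
| +0.4/0 | 0.5 | 0.5 × 0.4 = 0.20 | 26% | 0.20 SD, 25% |
| +0.4/0 | 0.3 | 0.3 × 0.4 = 0.12 | 12% | 0.13 SD, 13% |
| +0.3/+0.3 | either | 0 | 5% | about 0 SD, 4–6% |

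The documented rule was simulated as a whole-sample test at 5%, followed by a stabilized weight only if the test is significant. The ranges in the first two rows come from independent runs.

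**Why the weight does not help.**
- At +0.3/−0.3 the screen fires in only about 4 to 6% of trials. Forcing the whole-sample weight in every trial leaves subgroup imbalances of +0.30 and −0.30 with an overall imbalance of 0.00.
- At +0.4/0 the screen fires in about 73 to 74% of trials. Applying the weight in every trial gives about +0.21 and −0.20, so it creates imbalance in a subgroup that had none. Both subgroups shift by about 0.2, and their difference stays near 0.4.

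**T0 adjustment.** Suppose the covariate acts equally on the T0 and the six-month score, and the two scores correlate r. The false interaction becomes β(δ1 − δ0)(1 − r), with standard error 0.154√(1 − r²). For the worst row and r = 0.6: 0.30 × 0.4 = 0.12 SD, standard error 0.154 × 0.8 = 0.123, rejection about Φ(0.98 − 1.96) = 16%. Simulations that adjust for T0 gave about 0.06 to 0.12 SD and 6 to 16%. The result depends on r. In the worst row, r = 0.5 gives 0.15 SD and about 20%, and r = 0.7 gives 0.09 SD and about 13%.

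**Subgroup-specific score.** With subgroup-by-covariate terms in the propensity model, imbalance inside subgroups and the false interaction are both about 0.00 in every setting, and the test rejects in 2 to 5% of trials.

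**The case against.** **Reuse of one weight is inferred.** The article does not say that the weight is carried unchanged into subgroups, nor does it exclude re-estimation, and a fuller analysis plan may specify it. This stands as a limit on the claim. It does not remove the point, because the article prints a rule and a subgroup-specific step would have to depart from it.

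**The screen does most of the damage.** Where imbalances have opposite signs, usually no weight exists at all. This is correct, so the fix must address the screen as well as the weight. The 0.4/0 setting shows that the weight is also insufficient when it is triggered.

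**Harm is conditional.** It needs a prognostic covariate whose imbalance differs between subgroups. With equal imbalance the whole-sample weight works.

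**The longitudinal model may help.** Outcomes are measured from T0 to T4. T0 adjustment removes much of the bias, and a change-score analysis removes all of it if the covariate acts equally at both times. The article neither names the covariates nor says that the subgroup analyses use this model, so this reduces the size without settling the matter.

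**Two passages invite more than they support.** A reader might take "could lead to a selective clientele of patient e.g. disproportionately many breast cancer patients" (Limitations) as evidence that the arms differ. It describes the composition of the whole sample. A reader might also link this point to "subgroup analyses are planned to show which module of PIKKO works best for whom" (Strengths). That question concerns modules. Table 1 records module use in the intervention group only, apart from the ring folder, so a control-versus-intervention weight does not address it, and neither does the fix below.

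**Conclusion.** The point holds in a conditional form. As written, the procedure secures at best overall balance and can miss imbalance that differs between subgroups. Under the stated assumptions it can produce a false subgroup difference of about 0.12 to 0.31 SD with about 12 to 53% false-positive interactions. For scale, the planned main effect is 0.25 SD. T0 adjustment lowers this to about 0.06 to 0.12 SD and 6 to 16%, and equal imbalance to nothing. The imbalances, the covariate–outcome correlations and the T0-to-six-month correlation are all assumed.

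A reader might infer that the subgroup results are bound to be confounded, or that the trial's main conclusion is at risk. The document supports neither. It gives no evidence of imbalance that differs by subgroup, and this mechanism leaves the six-month primary comparison and the 338, 676 and 1014 untouched. The weakness lies in secondary analyses and is cheap to correct.

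**What to change.** In Statistical methods, state for each subgroup factor that:

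- the propensity score is estimated from the pre-treatment variables regardless of whole-group significance, with subgroup-by-covariate terms (or separately within subgroups);
- standardized differences are checked inside each subgroup, against a stated limit such as 0.1;
- effect modification is tested as a group-by-subgroup term in a weighted model that adjusts for the T0 score;
- the results are labelled exploratory, and only descriptive results are given where balance is not reached.

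The exploratory label is also warranted by precision. With 169 per cell, a true interaction of 0.25 SD has power of only Φ(0.25/0.154 − 1.96), about 37%, before any adjustment for T0.

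The cost is wording and some extra modelling. No new data are needed and the sample size does not change. The downside is more variable weights and wider intervals in small subgroups.

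### Agreement between the analyses with and without imputation is called validation, yet a six-month MCS difference could pass both planned dropout checks while biased if dropout rates are similar but reasons for leaving differ by group

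*Protocol article*

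**What the plan says.** All references are to the Protocol article.

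- **Dropout model (Statistical methods).** Dropout is examined by "a logistic regression with dropout as criterion and group assignment and baseline variables as predictors", with the propensity-based weights applied. A Cox regression is also named, without its event or covariates.
- **Imputation comparison (Statistical methods).** "To validate our analyses, we will conduct the analyses with imputed missing data and without imputation". The imputation method is missForest (Imputation procedure for missing data). The article does not list the variables that enter it.
- **Reasons for leaving (Participant withdrawal and other drop-outs).** "Possible reasons may be deterioration of health or consideration of the questionnaires as an additional burden".
- **Amount of loss (Sample size calculation).** "The expected dropout rate was 33.3% regarding the baseline (338 of 1014"), split equally by group: "338 reaching the end point + 169 dropout".
- **Control-only exit (Participant timeline; Changing from control to intervention).** A control patient may switch to the intervention, and the control questionnaires then end. Intervention patients have no such route.
- **Data available before the endpoint (Table 1).** SF-12, PHQ-9 and changes in the cancer are collected at three months (T1). The primary endpoint is at six months (T2).

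**The concern.** Worsening health is a change after baseline. A dropout model with baseline predictors can show who was likely to leave from the start, but not who left because they got worse. The imputed analysis fills gaps by prediction from returned data, and the unimputed analysis uses returned data directly. If patients leave because of a change after their last returned form, neither analysis has seen that change, and the two can agree on the same wrong answer.

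This biases the group comparison only if the selection differs between groups. The documents give one reason why it might: the switching exit. By the Trial status section, control recruitment ended on 31 October 2018 and the intervention period followed. Controls enrolled from about May 2018 therefore reached T2 after switching became possible. With a third of T2 outcomes expected missing in a non-randomized comparison, the report could describe the primary result as validated when the planned checks had no means of finding the problem.

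**Working it through.** **1. The plan's own figure.** Inputs from Sample size calculation: the effect and the test are given as "expected effect of d = 0.25 for a two-sided t-test with same sized comparative groups". The error rates are a 5% type I error and 90% power.

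- Normal approximation: n = 2 × (1.960 + 1.282)² / 0.25² = 336.2, so 337 per group.
- Exact noncentral t: 338 per group, power 0.9007. This agrees with "only 676 participants (338 per group) of the patient questionnaires are required to the statistical analyses".
- Dropout: 338 / (1 − 1/3) = 507 per group, 1014 in total.

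The stated figures reproduce.

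**2. How small a departure matters.** This step uses only those figures. Suppose d = 0.25 is observed with 338 per group, and that prediction for the lost patients would give the same difference.

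- SE of d = √(2/338 + 0.25²/(4 × 338)) = 0.0772.
- Lower 95% limit = 0.25 − 1.96 × 0.0772 = 0.0986.
- If the lost third of the intervention group scores δ SD below prediction, the overall difference falls by δ/3. Holding the SE fixed, significance goes when δ/3 = 0.0986, so δ = 0.296, or about 0.30 SD.

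**3. Can the two checks see such a departure?** Simulations used 507 per group, no true effect, standardised scores, all T1 forms returned, and regression imputation from baseline and T1 as a stand-in for missForest. Correlations (0.6 between visits unless stated) and dropout slopes are assumptions; the article gives none. Slopes are log-odds per SD.

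*(a) Equal loss of 33.3%. Controls leave at random; intervention patients leave by how far T2 falls below what baseline predicts.*

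| Slope | Bias, no imputation | Bias, imputed | Group term flags | Baseline term flags | Mean gap between runs |
|---|---|---|---|---|---|
| 0.5 | 0.12 SD | 0.10 SD | 6% | 3% | 0.03 SD |
| 1.0 | 0.22 SD | 0.19 SD | 4% | 5% | 0.03 SD |
| 1.5 | 0.29 SD | 0.25 SD | 6% | 4% | 0.04 SD |

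The dropout model flags at about the chance rate. The gap between the runs is close to the 0.02 to 0.03 SD seen when there is no bias. The t-test without imputation rejects in 33% to 97% of runs. With imputation it rejects in 44% to 97%, but part of that comes from single imputation, which rejected in 11% to 12% of runs even without bias.

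*(b) Equal loss, driven by deterioration after T1, in controls only* (slope 1.0; correlations 0.6, 0.65 and 0.5). Bias is −0.20 SD in both runs, and −0.21 and −0.21 SD in a repeat. The runs agree and are equally wrong.

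*(c) Equal loss, driven by T1 status in one group only.* Bias is 0.04 to 0.11 SD without imputation and about 0 with imputation that uses T1. It remains 0.04 to 0.11 SD if imputation uses baseline only.

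*(d) Unequal rates, same deterioration mechanism in both groups.* At 28.3% against 38.3%, bias is 0.04 to 0.08 SD and the group term flags 92% to 93% of runs. Its power for a gap of 3, 5, 7, 10 or 15 points is 17%, 39%, 66%, 92% or 99.9%.

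*(e) Equal rates, same mechanism in both groups.* No bias.

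**The case against.** A reader might infer that any T2 effect distorted by unequal loss would pass both checks. The documents do not support that. Group is a predictor in the dropout model, so a difference in rates is tested, with good power for a 10-point gap (3d). The control-only switch would tend to appear there, although the term cannot tell whether it biased T2. Loss driven by T1 is corrected, and shows as a gap between the runs, if T1 enters the imputation (3c). The growth curve model can also use T1.

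A reader might also infer that the dropout model has main effects only and that T1 data are ignored. That would rest on silence. A condensed article names predictors in one clause, and interactions may stand in the full plan. Reasons for withdrawal are also asked for, and the enrolling person is contacted when a form is not returned.

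The simulated cases depend on how deterioration is defined. In (a), it is the part of the change not predicted by baseline. If loss follows the raw score change, baseline MCS can itself predict dropout. In a T1 version with loss in controls, the baseline term was significant in 82% of runs, bias was about −0.05 SD, and the t-test rejected in 8%.

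Finally, the documents do not say that navigators keep deteriorating patients in the survey; they give navigators only the baseline form to hand out. The direction of any bias is therefore unknown. A richer dropout model or return-probability weights would not cure case (b): weighting with baseline and T1 interactions still left −0.20 SD.

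All of this narrows the point. What remains is the stated claim of validation, which no dropout model built on returned data can justify.

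**Conclusion.** The concern holds in a limited form. Comparing results with and without imputation cannot validate the primary result against loss that depends on change after the last returned form. A T2 MCS difference could pass both planned checks while biased if dropout rates are similar, the reasons for leaving differ by group, and those reasons act after that form. Under strong but not extreme assumptions, the bias can reach the size of the planned effect. With the same mechanism in both groups it is nil.

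The bias sizes rest on assumed correlations, slopes and one-sided selection. The tipping point of about 0.30 SD rests only on the article's sample size figures, a fixed SE and the supposition that d = 0.25 is observed. Nothing here shows that such loss occurred. The finding is that the plan, as stated, would call the result validated without having tested for it.

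**What to change.** 1. In Statistical methods, stop describing the comparison with and without imputation as validation. Report it as two analyses that both rely on returned data.
2. Add a tipping-point analysis of the primary T2 MCS comparison. Shift the values assigned to lost patients in one group at a time, for example from 0 to 0.5 SD and in both directions, and report the shift at which the conclusion changes.
3. State that T1 SF-12, T1 PHQ-9 and reported cancer changes enter the imputation model. This secures the correction in case 3(c).
4. Add these variables and their interactions with group to the dropout model, for loss between T1 and T2 among patients who returned T1. This describes differential loss better but does not replace step 2.

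All variables are already collected, and design and recruitment do not change. The cost is some analysis work and possibly a more cautious conclusion.
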